## Abstract

**Background:**

During the last decade online interventions have emerged as a promising approach for patients with mild/moderate depressive symptoms, reaching at large populations and representing cost-effective alternatives. The main objective of this double-blind, randomized controlled trial is to examine the efficacy of an internet-based self-management tool (iFightDepression) for mild to moderate depression as an add-on to treatment as usual (TAU) versus internet-based psychoeducation plus TAU.

**Methods:**

A total of 310 participants with major depression disorder (MDD) will be recruited at four different mental-health facilities in Spain. Participants will be randomly allocated to one of two study arms: iFightDepression (iFD) tool + TAU vs. internet-based psychoeducation + TAU. Both interventions last for 8 weeks and there is a 12 weeks follow up. The primary outcome measure is changes in depressive symptoms assessed with the Hamilton Depression Rating Scale. Additionally, pre-post interventions assessments will include socio-demographic data, a brief medical and clinical history and self-reported measures of depressive symptoms, quality of life, functional impairments and satisfaction with the iFD tool.

**Discussion:**

iFightDepression is an easy-prescribed tool that could increase the efficacy of conventional treatment and potentially reach untreated patients, shortening waiting lists to receive psychological treatment. Confirming the efficacy of the iFD internet-based self-management tool as an add-on treatment for individuals with mild to moderate depression will be clinically-relevant.

**Trial registration:**

Registration number NCT02312583. Clinicaltrials.gov. December 4, 2014.

## Background

According to the World Health Organization (WHO) predictions, by 2030 depression will be the leading cause of disease burden globally. Depression is not only associated with disability and with enormous individual impairments, but also it entails high economic cost for society [1, 2].

Depression is a recurrent disorder, meaning that one individual will suffer an average of four depressive episodes during his/her life [3]. Establishing an effective treatment at the early stages of the disease is fundamental for the successful prognosis of the disorder [4]. Although several treatment options have been developed for depression, a large proportion of individuals do not have access to these treatments and some of them remain untreated [5]. Furthermore, contrary to what is suggested in international guidelines for the management of mild and moderate depression symptoms, the majority of General Practitioners (GPs) tend to prescribe antidepressant medications [6, 7].

In this context, online interventions appear as promising treatment approaches that can reach a large majority of patients [8, 9], while at the same time, representing cost-effective alternatives [10]. For clients, internet-based programs offer some advantages. These include: anonymity, avoiding the stigma associated with seeing a therapist and the option to do the treatment at any time and place, at the client’s own pace, for example, at home [11, 12]. Therapist involvement depends on the intervention, but in general, most programs aim at decreasing the therapist workload. Most internet-based treatments are framed in cognitive behavioral therapy (CBT) and are developed to treat individuals with mild to moderate depressive symptoms that are usually visited in primary care settings. In a meta-analysis of randomized-controlled trials comparing the effects of guided self-help and face-to-face psychotherapies, it was concluded that both interventions have comparable effects. Thus, recommending the implementation of guided self-help interventions in routine care [13].

In the context of the European project Preventing Depression and Improving Awareness through Networking in the European Union (PREDI-NU) [14], the European Alliance Against Depression (EAAD) created the iFightDepression (iFD) tool. The EAAD is a consortium of different countries around the world that use an evidence-based approach for improving care of depressed persons and prevent suicidal behavior [15]. IFD is an internet-based self-management tool for moderate to mild depression designed as a complementary intervention to standard care. IFD is based on cognitive behavioral therapy and structured in seven different modules.

### Study objectives

The aim of this double blind, randomized controlled trial (RCT) is to examine the efficacy of the iFightDepression as an add-on to treatment as usual (TAU) for patients with mild to moderate depressive symptoms versus internet-based psychoeducation plus TAU. The primary outcome measure will be changes in depressive symptoms as measured with the Hamilton Depression Rating Scale [16]. Secondly, we aim at examining the effects of this intervention on other variables including quality of life and functioning.

## Methods

### Design

We designed an 8-week, double-blind, randomized controlled trial, with two treatment arms: iFightDepression tool + TAU and internet-based psychoeducation + TAU. Participants will be randomly allocated (1:1) after the first assessment visit. Randomization will be performed electronically by an independent study researcher. Participants in both treatment arms will be followed via internet during a 12-week period.

### Study participants

A total of 310 participants with major depressive disorder (MDD) diagnosis will be included in the study. Diagnosis will be made according DSM-IV-TR criteria and participants will be recruited from different mental health services (i.e., Red de Salud Mental de Guipúzkoa, Hospital del Mar, Hospital de la Santa Creu i Sant Pau, Hospital Parc Taulí and Hospital Universitario de la Princesa) and primary care facilities in their catchment areas. Sample size was established in order to detect an effect size of d = 0.2 with 95% power (SE = 0.5) and assuming a conservative correlation coefficient between pre-post measures of 0.5 and a drop-out of 20%. Sample size was calculated using G*Power 3.1.7 software.

Individuals meeting the following criteria will be eligible: 1) Participants of both genders 18 years old and older, 2) MDD diagnosis according to DSM-IV-TR criteria with mild-moderate symptoms according to the CGI-severity (scores ≤4), 3) minimum knowledge of internet use and availability of an internet device (tablet, computer, smartphone) and 3) given written informed consent. Exclusion criteria are: 1) suicidal ideation assessed by the HDRS and/or clinical interview, 2) psychotic symptoms related or not related to a mood disorder, 3) severe comorbidity axis I and axis II diagnosis, 4) currently receiving standard face-to-face CBT.

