### Statistical analysis plan

SPSS v22.0 will be used for statistical analyses. Primary analyses will be conducted on the Intention-To-Treat (ITT) sample. Missing data will be inspected and handled via full information maximum likelihood (FIML) or multiple imputations (MI) as appropriate.

The primary outcome is change in HDRS scores from baseline to post-treatment (8 weeks). For primary and secondary outcome measures, repeated measures ANOVAs will be computed to examine pre-post treatment differences between groups.

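### The sample of 310 does not give 95% power for d = 0.2: the planned repeated measures ANOVA has about 35% power at that effect

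*Protocol article*

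**What the plan says.** The protocol article, Study participants, fixes the total: "A total of 310 participants with major depressive disorder (MDD) diagnosis will be included in the study". It justifies the total as follows: "Sample size was established in order to detect an effect size of d = 0.2 with 95% power (SE = 0.5"), "assuming a conservative correlation coefficient between pre-post measures of 0.5 and a drop-out of 20" per cent. It adds: "Sample size was calculated using G*Power 3.1.7 software". It does not name the G*Power routine.

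The Design section sets equal allocation: "Participants will be randomly allocated (1:1) after the first assessment visit". The Statistical analysis plan section defines the endpoint, "The primary outcome is change in HDRS scores from baseline to post-treatment (8 weeks"), and the test: "repeated measures ANOVAs will be computed to examine pre-post treatment differences between groups". Table 2 lists the HDRS at two visits only, baseline and post-intervention.

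**The concern.** A standardised difference of 0.2 between two parallel arms is small. Detecting it with 95% power normally takes well over a thousand patients unless the baseline explains nearly all of the outcome variance, and a pre-post correlation of 0.5 is far from that. A total of 310 is too small by a factor of about five, so rounding cannot explain the gap.

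The power statement for the primary endpoint is at stake. Both arms receive treatment as usual and the comparator is itself an online programme, so a small between-arm difference is a realistic possibility. The article credits the trial with near-certain detection of a difference that the planned test would usually miss.

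**Working it through.** **Inputs from the protocol article.** Total N = 310, d = 0.2, power 95%, correlation ρ = 0.5 and drop-out 20% (Study participants); 1:1 allocation (Design); two-group comparison of HDRS change over two measurements (Statistical analysis plan; Table 2). Completers: 310 × 0.8 = 248. **Assumed:** two-sided alpha 0.05, with alternatives in step 5.

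**1. Reduce the planned test.** With two measurements, the time-by-group test in a repeated measures ANOVA is a two-sample t-test on change. Its variance is Var(change) = 2(1 − ρ)SD² = 2 × 0.5 × SD² = SD². So d = 0.2 means the same whether it is scaled by the raw SD or by the SD of change.

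**2. Try to reproduce 310 from the stated inputs.** Normal approximation: N = 4(1.960 + 1.645)²/0.2² = 4 × 12.996/0.04 ≈ 1,300. The noncentral t gives 1,302. Enrolled: 1,302/0.8 = 1,628. For ANCOVA the variance factor is 1 − ρ² = 0.75, giving 978 completers and 978/0.8 = 1,223 enrolled. Neither is near 310.

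**3. Power of the planned sample at d = 0.2.** With 248 completers the noncentrality is 0.2 × √(248/4) = 1.575, and Φ(1.575 − 1.960) = 0.350. With 310 it is 0.2 × √(310/4) = 1.761, and Φ(1.761 − 1.960) = 0.421. The noncentral t results are:

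| | 248 completers | all 310 |
|---|---|---|
| Repeated measures ANOVA (planned) | 34.8% | 41.9% |
| ANCOVA | 44.1% | 52.7% |

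**4. Detectable difference with 248 completers.** At 95% power: 3.605 × √(4/248) = 0.458, reported as 0.46. At 80% power: 2.802 × √(4/248) = 0.356, reported as 0.36. Multiplying by √0.75 = 0.866 gives 0.40 and 0.31 for ANCOVA.

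**5. More lenient readings of the stated inputs.**
- One-sided alpha 0.05, ANCOVA, no drop-out: 65% power.
- One-sided alpha 0.10, ANCOVA, no drop-out: 77% power.
- Target lowered to 80% power: 788 completers, or 592 with ANCOVA.
- Higher correlation: the planned test with 248 completers reaches 95% only at ρ of about 0.91.
- Paired t-test at d = 0.2, which has no control comparison: 327, or 409 after drop-out.

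**6. Where a figure near 310 could come from.**
- *0.2 entered as Cohen's f.* For two equal groups d = 2f = 0.4. G*Power's repeated measures between-factors routine with m = 2 uses λ = f²Nm/(1 + (m − 1)ρ) = 0.04 × 2N/1.5 = 0.0533N. This gives N = 246 for 95% power, and 246/0.8 = 307.5, so 308.
- *0.2 as a raw difference with SD 0.5.* Then d = 0.2/0.5 = 0.4. ANCOVA gives λ = 0.4²N/(4 × 0.75) = 0.0533N, which is the same noncentrality and again 246 and 308. The normal formula gives 244 and 305.
- *Interaction entry f = 0.1 with three measurements.* This gives 260, and 260 × 1.2 = 312. It does not match the design, because the HDRS is measured twice and the drop-out allowance should be a division by 0.8 (325).
- *Interaction entry with two measurements.* f = 0.1 gives 328 (410 enrolled) and f = 0.2 gives 84 (105 enrolled). Neither fits.

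The first two routes both imply d = 0.4. At d = 0.4 with 248 completers, power is 88% for the planned repeated measures ANOVA and 95% for ANCOVA.

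**The case against.** The strongest defence is that the trial may be sized about right and the effect mislabelled. If d = 0.4 was intended, the planned test has 88% power, and ANCOVA would reach 95%. That stands. It is why the remedy keeps 310, but it does not make the printed claim for d = 0.2 true.

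Four stronger readings are tempting, and the article does not support them.

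- **That 310 can only come from entering 0.2 as Cohen's f.** A raw difference of 0.2 over an SD of 0.5 with ANCOVA gives the same 308. Nothing in the article separates the two, and neither gives exactly 310.
- **That the sample size was computed for the wrong effect, the group difference averaged over baseline and week 8.** The between-factors routine does test that, but the article does not say this routine was used. It remains a hypothesis. For the same reason the SE of 0.5 cannot be called irrelevant: if it is a mislabelled SD, it is a needed input. All that can be said is that it is undefined.
- **That the absent alpha is itself a defect.** A condensed article may leave alpha, sidedness and the choice of routine to the full protocol or analysis plan. Alpha is an assumption here, not a finding.
- **That a null result would be read as excluding d = 0.2.** The article does not say how a null result will be interpreted.

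It could also be argued that the planned maximum likelihood or multiple imputation would recover information lost to drop-out. The most that could achieve is the full-data figure for 310, which is 42%.

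**Conclusion.** The power statement is wrong as written. For the planned test, power at d = 0.2 is about 35% with 248 completers and at most 42% with 310, against the stated 95%. Delivering 95% at d = 0.2 would take about 1,302 completers (about 1,628 enrolled), roughly five times the planned number.

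This rests on ρ = 0.5, 20% drop-out and 1:1 allocation, all stated, and on two-sided alpha 0.05, which is assumed. No variant in step 5 that keeps d = 0.2 and ρ = 0.5 reaches 95%; the most lenient gives 77%.

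It is not established how 310 arose. An intended d = 0.4 is the most plausible explanation. A reader might infer a grossly undersized trial, but the article supports only the narrower conclusion that the stated effect, power and sample size are incompatible.

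**What to change.** Keep 310 and make the statement in Study participants match the test in the Statistical analysis plan section. Choose one of the following:

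1. **Planned test kept.** Replace the sentence with: *With 248 completers, two-sided alpha 0.05 and a baseline-to-week-8 correlation of 0.5, the repeated measures ANOVA has 95% power for d = 0.46, 80% power for d = 0.36 and 35% power for d = 0.2.*
2. **Analysis changed openly.** Amend the primary analysis to ANCOVA of week-8 HDRS adjusted for baseline, and state 95% power for d = 0.40, 80% for d = 0.31 and 44% for d = 0.2. These figures must not be quoted while repeated measures ANOVA remains the primary test, because they would overstate its power.

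In either case, define or correct the SE of 0.5 after checking the original G*Power entry; do not simply delete it.

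Cost: wording only, plus a declared analysis change under option 2. The stated detectable effect becomes less favourable. No extra patients are needed.

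### The sample-size statement gives an undefined SE = 0.5 where a significance level would be expected, so 310 participants and 95% power cannot be reproduced as printed

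*Protocol article*

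**What the plan says.** The protocol article, Study participants, sets the total at 310 and lists what went into it. The trial is sized "to detect an effect size of d = 0.2" "with 95% power (SE = 0.5"), with a "conservative correlation coefficient between pre-post measures of 0.5" and 20% drop-out. It adds: "Sample size was calculated using G*Power 3.1.7 software". Allocation is 1:1 (Design). The abbreviation SE is not explained there or in the abbreviation list, and 0.5 carries no unit. No type I error rate or sidedness appears anywhere in the article.

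The analysis section names the planned test: "repeated measures ANOVAs will be computed to examine pre-post treatment differences between groups". That sentence is used below only to identify the test. It contains no error.

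**The concern.** A sample size calculated from an effect size, a power and a correlation also needs a significance level. The statement has an unexplained SE of 0.5 beside the power, where the level would normally stand. A reader who wants to check the 310 therefore lacks one input and has another that cannot be interpreted.

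At stake is the planning claim. A power of 95% means something only together with the alpha, the test and the effect-size metric used to compute it. If those are not recorded correctly, nobody can tell whether the trial was sized for the effect it names.

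**Working it through.** **Inputs from the article.** Total 310; drop-out 20%, so completers = 310 × 0.8 = 248 (124 per arm); d = 0.2; power 0.95; pre-post correlation ρ = 0.5; two arms, 1:1; two time points for the HDRS (m = 2). For two equal groups Cohen's f = d/2, so d = 0.2 is f = 0.1.

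**Formulas.** Repeated-measures ANOVA, noncentral F with 1 and N − 2 degrees of freedom:
- group-by-time interaction: λ = f²·N·m/(1 − ρ)
- between-factor test: λ = f²·N·m/(1 + (m − 1)ρ)

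Two-sample comparison of change scores: with ρ = 0.5 the SD of change equals the SD, so SE(d) = 2/√N and λ = d²N/4. Drop-out is added as N/0.8.

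**Step 1: what reproduces 310?** Of the runs made at 95% power with drop-out added, one comes close: alpha 0.05, between-factor test, with 0.2 entered as f and not as d. Then λ = 0.04 × 246 × 2/1.5 = 13.12, which gives 95% power at N = 246, and 246/0.8 = 307.5, or 308. Entering 0.2 as f is equivalent to d = 0.4.

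**Step 2: 0.5 read as alpha (power 0.95).**

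| Test | Effect | Completers | With drop-out |
|---|---|---|---|
| Interaction | f = 0.1 | 134 | 168 |
| Between-factor | f = 0.1 | 400 | 500 |
| Interaction | f = 0.2 | 34 | 43 |
| Between-factor | f = 0.2 | 100 | 125 |
| Two-sample t, two-sided | d = 0.2 | 532 | 665 |
| Two-sample t, one-sided | d = 0.2 | 272 | 340 |

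None is 310.

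**Step 3: 0.5 read as a standard error in SD units.** SE(d) = 2/√248 = 0.127. Setting 2/√N = 0.5 gives N = 16, or 8 per arm. This does not fit 310.

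**Step 4: 0.5 read as a standard error in HDRS points.** The implied SD of change is 0.5/√(2/124) = 3.9 with 124 per arm, or 0.5/√(2/155) = 4.4 with 155 per arm. This is arithmetically possible, but the article gives no SD or unit that would confirm it.

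**Step 5: 0.5 read as an SD, with a raw difference of 0.2.** At two-sided 0.05 this needs 326 completers, or 408 with drop-out. That is not 310.

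**Step 6: what the stated d = 0.2 gives at an assumed two-sided alpha of 0.05.**

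| Test | λ at N = 248 | Power at 248 | N for 95% | With drop-out |
|---|---|---|---|---|
| Interaction, f = 0.1 | 0.01 × 248 × 2/0.5 = 9.92 | 88% | 328 | 410 |
| Between-factor, f = 0.1 | 0.01 × 248 × 2/1.5 = 3.31 | 44% | 978 | 1,223 |
| Change-score comparison, d = 0.2 | 0.04 × 248/4 = 2.48 | 35% | about 1,300 | about 1,625 |

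The first and third rows differ because they measure the effect differently. The interaction formula with f = 0.1 has λ = 0.04N, while the change-score comparison with d = 0.2 has λ = 0.01N. The first therefore assumes a difference in change twice as large (√4 = 2). This is why the metric has to be named along with alpha.

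**The case against.** The strongest reply is that this is a small slip in a condensed article. The figure stands in a planning sentence and is not an analysis rule. The full protocol and any statistical analysis plan are not shown, and a test level is commonly left to them. The near match at alpha 0.05 suggests that a conventional level was used and only its label or a digit went wrong. Inserting 0.05 would also leave the larger problem in place, since d = 0.2 still does not lead to 310.

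Most of this stands, and it rules out several stronger readings that a reader might infer:
- **That the trial operates at a 50% false-positive rate.** Nothing labels 0.5 as alpha, and step 2 shows that an alpha of 0.5 does not produce 310.
- **That the primary test has no valid decision threshold.** The article states none, but a document not shown may fix it. Its absence from the analysis section is not a finding.
- **That the value is impossible on any reading.** Step 4 shows that a standard error in HDRS points cannot be excluded. The value is undefined, which is a lesser charge.
- **That this is the only error-rate input.** The 95% power itself fixes the type II error at 0.05.

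The reply does not remove the defect. The article chose to print its inputs, and one of them cannot be interpreted. An unseen document does not make a wrong figure in the published statement right.

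**Conclusion.** The point holds as a defect of the sample-size statement in Study participants. SE = 0.5 is undefined. It does not reproduce 310 as an alpha or as a standardised standard error, and no alpha is stated, so the 95% power cannot be reproduced as printed. A misprint for an error level of 0.05 is the likeliest explanation, but it rests on one reconstruction (308 against 310) that also requires 0.2 to be Cohen's f and the between-factor test to be the one used. The article says neither.

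Correcting alpha alone does not rescue the claim. At an assumed two-sided 0.05 and the stated d = 0.2, 248 completers give 88%, 44% or 35% power, depending on the test and metric. These figures assume ρ = 0.5, equal arms and an analysis of completers. The article does not support any conclusion about the error rate at which the trial will actually be judged.

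**What to change.** In Study participants, replace the SE entry with the alpha and sidedness actually entered in G*Power. In the same sentence name the test family (between-factor, interaction or two-sample) and say whether 0.2 is d or f. Then restate the power that 248 completers deliver at that level for the stated d = 0.2. If the level was two-sided 0.05, the figure is about 88% (interaction formula, f = 0.1), 44% (between-factor) or 35% (change-score comparison), according to the test named.

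The cost is a few lines of text and a look at the saved G*Power output. Enrolment and conduct do not change.

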### Procedure

Eligible participants will be identified through the different sites by a case manager, mainly, by the participant’s general practitioner. However, other professionals (i.e., psychiatrist, psychologist or community mental health nurses) with experience in the assessment and diagnosis of depression would be also able to refer participants to the study. These professionals will verify inclusion/exclusion criteria and will inform patients about the study. Participants who confirm their interest in participating, will be contacted by phone within 1 week to schedule the first assessment visit (face-to-face). Each site will designate a highly trained psychologist who will conduct the first face-to-face visit in order to confirm that participants met inclusion/exclusion criteria and to obtain the written informed consent. Participant’s assessment will be recorded in the electronic Case Report Form (e-CRF). In this assessment visit, and regardless of the treatment arm the patient will be assigned to, the second face-to-face assessment visit (week 8) will be booked. Randomization to one of the two conditions (i.e., iFightDepression tool + TAU or internet-based psychoeducation + TAU) will be electronically performed by the e-CRF once the patient data is introduced. The researcher who conducts assessment visits will remain blind to participant’s allocation. After the first visit, participants in both arms will received an email with instructions to be followed. The intervention group will receive instructions to create an account and to work within the iFD tool. In addition, the intervention group will receive a telephone call to make sure that participants activated successfully their user accounts. Then, they will be contacted bi-weekly by a mental health professional (specialized nurse or psychologist), to work through the material and to provide technical support). During the 8 weeks of the trail all participants will be follow-up by e-mail in order to complete the PHQ-9 and RDQ. Participants will have to complete the PHQ-9 and the RDQ again at week 12. The study protocol was developed in accordance with the SPIRIT (Standard Protocol Items: Recommendations for Interventional Trials) guidelines [17]. A flowchart of participants is shown in Fig. 1.

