For the purpose of this study and to facilitate the recruitment, the IFD tool is available in three languages: Spanish, Catalan and Basque, and patients are allowed to choose among versions according to their language preferences. Participants can access the PHQ-9 at any time, to assess their depression symptoms. A guide for interpreting the PHQ-9 scores is provided. If the patient responds positively to the item regarding suicide (i.e., “Thoughts that you would be better off dead or of hurting yourself in some way”) a message recommending seeking for emergency care will appear on the top of the screen. In addition, emergency contacts for Spain are listed on the website. The use of IDF tool is complementary to TAU which consists of monthly visits with the GP and pharmacological treatment with an ISRSS if needed.

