#### Active control group (internet-based psychoeducation + TAU)

Internet-based psychoeducation consists of a webpage containing information about MDD and healthy habits. This webpage (www.ifightdepression.com) was also designed by the EAAD consortium, and unlike the tool, workshops and tasks are lacking. The psychoeducative content of this website is restricted to information regarding healthy habits (healthy eating, physical activity, positive social contact and daily organization). In addition, information on the following topics is included: what is depression, signs and symptoms, diagnosing depression, subtypes of depression, brain function in depression, causes and an overview of depressions treatment (both pharmacological and psychological). Participants on this condition can also complete the online PHQ-9. This is an open-access webpage (i.e., a username and password are not required). Participants allocated to this condition will receive an e-mail with the page link and will be instructed to navigate freely throughout their content. As in the intervention group, TAU consists of monthly visits to the GP together with pharmacological treatment (if needed).

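### Exclusion 4 bars concurrent CBT only when it is face-to-face, so users of internet or telephone CBT, or of iFD itself, can be randomised to either arm

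*Protocol article*

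**What the plan says.** The protocol article lists four exclusions under Study participants. The fourth is the only one that concerns psychological treatment: "4) currently receiving standard face-to-face CBT". It is limited by delivery format (face-to-face) and by time (current).

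The Background section describes the tested tool: "IFD is based on cognitive behavioral therapy and structured in seven different modules". It is delivered over the internet.

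The background care is described in the same way for both arms. For the intervention arm it is "TAU which consists of monthly visits with the GP and pharmacological treatment with an ISRSS if needed". For the control arm: "As in the intervention group, TAU consists of monthly visits to the GP together with pharmacological treatment (if needed". Neither sentence mentions psychological treatment, either as part of usual care or as something ruled out.

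Under Procedure, candidates come mainly through the general practitioner, but referral is also open to "other professionals (i.e., psychiatrist, psychologist or community mental health nurses) with experience in the assessment and diagnosis of depression". Study participants names hospital and mental health services as recruiting sites, along with primary care in their catchment areas.

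**The concern.** Exclusion 4 shows that the sponsor wants patients already in CBT kept out. The format it names is not the one under test. A patient on another internet CBT programme, or on iFD itself, is closer to the tested intervention than a patient in face-to-face CBT, yet only the latter is excluded.

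If such a patient is allocated to control, the comparator contains the ingredient that the trial means to withhold. If allocated to iFD, the patient receives a second course of similar material. Either way the two arms differ less in CBT exposure than the design intends. The HDRS difference at week 8 can then shrink, and with a planned effect as small as d = 0.2 there is little room for that.

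**Working it through.** **Step 1. Read the criteria literally.** The inclusion criteria concern age, an MDD diagnosis with CGI-severity of at most 4, internet knowledge and a device, and consent. Exclusions 1 to 3 concern suicidal ideation, psychotic symptoms and severe comorbidity. None of these turns on psychological treatment, so exclusion 4 decides alone:

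| Patient at first visit | Caught by exclusion 4? |
|---|---|
| Current face-to-face CBT | Yes |
| Current telephone CBT | No |
| Current internet CBT, other programme | No |
| Current or previous iFD user | No |

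**Step 2. Compare with usual care.** TAU is described by what it contains: GP visits and medication if needed. A patient on internet CBT is receiving something outside that description. The description does not prohibit it, so the two statements are in tension but both can be true.

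**Step 3. Look for a later safeguard.** The clinical history under Study measures names current pharmacological treatment but not psychological treatment. The Discussion plans a sub-analysis for antidepressants only. Under Procedure, "The intervention group will receive instructions to create an account and to work within the iFD tool"; nothing printed asks about an existing or earlier account. Table 2 does schedule a medical/psychiatric history at baseline and post-intervention, so there is a place to record such treatment, but no stated item.

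**Step 4. Illustrate the possible size.**

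*Inputs from the protocol:* d = 0.2, power 95%, pre-post correlation 0.5, dropout 20%, N = 310, 1:1 allocation. *Assumed:* two-sided alpha 0.05 (not stated); a share q in each arm already on similar CBT; no further gain from iFD for that share.

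*The plan's own figure.* The group-by-time test in a two-group, two-occasion repeated measures ANOVA has noncentrality λ = N f² m/(1 − ρ), with f = d/2 = 0.1, m = 2 and ρ = 0.5. At 95% power it needs 328 completers, or 328/0.8 = 410 enrolled. The stated 310 is not reproduced. That is a separate matter and does not support this point.

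*Attenuation.* d(q) = 0.2(1 − q). The sample needed for the same power rises by 1/(1 − q)². Power is shown for 310 × 0.8 = 248 completers, where λ = 248 × 0.01(1 − q)² × 2/0.5 = 9.92(1 − q)².

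| q | d | 1/(1 − q)² | λ | Power, 248 completers |
|---|---|---|---|---|
| 0 | 0.20 | 1.00 | 9.92 | 88.0% |
| 5% | 0.19 | 1.11 | 8.95 | 84.6% |
| 10% | 0.18 | 1.23 | 8.04 | 80.6% |
| 20% | 0.16 | 1.56 | 6.35 | 70.9% |

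The power levels depend on taking f = d/2. A plain two-sample comparison of d = 0.2 at 95% power would need 1,300 completers in total. The columns for d and 1/(1 − q)² do not depend on that choice and are the ones to use.

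*A milder assumption.* If the affected share kept half of the benefit, d = 0.2(1 − q/2): 0.2 × 0.95 = 0.19 at q = 10%, and 0.2 × 0.90 = 0.18 at q = 20%.

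**The case against.** **The article is a condensation.** The full protocol may carry fuller eligibility and concomitant-care rules, and silence in an article is not a fault. That stands for concomitant care in general. It does not dispose of exclusion 4, which is printed in specific words that draw a line by format.

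**There is no contradiction with TAU.** A reader might infer that admitting internet CBT users contradicts the TAU description. The documents do not support this. They say what usual care consists of, in both arms alike, and never say that other psychological care is barred. This objection stands in full.

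**Such patients may be rare.** Recruitment is mainly through general practice, and the Discussion describes the people the tool could reach as often untreated or waiting for psychological care. No passage says that internet or telephone CBT is common at these sites. Prior iFD use is also speculative: the Spanish, Catalan and Basque versions are presented as serving this study's recruitment, and intervention participants set up accounts after allocation. The open control page is distinct from the tool: "This is an open-access webpage (i.e., a username and password are not required". All this stands, and it is why no size can be claimed.

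**Zero further benefit is the extreme case.** iFD also brings bi-weekly contact with a professional, which could help even a patient already doing CBT. This stands; the milder assumption above halves the attenuation.

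**The design is naturalistic.** Tolerating background care is reasonable in an add-on trial. The argument is weak here because concurrent CBT in one format is already excluded, and no reason is given for admitting the others.

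**The fix still admits other psychotherapies.** True. It completes the aim of exclusion 4, which is about CBT, and does not try to make the sample match TAU exactly.

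**Conclusion.** The point holds in a limited form. As written, exclusion 4 admits people already using internet or telephone CBT, or iFD itself, to a trial of internet-delivered CBT, and no printed safeguard identifies them. This can attenuate the between-arm HDRS difference and reduce power.

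Two stronger readings are not supported. The documents do not show that dilution will occur: they give no prevalence, and the share may be small. Nor would the result be tilted toward either arm, since 1:1 randomisation balances these patients in expectation.

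The illustration (d falling from 0.2 to 0.19 at a 5% share, or 0.18 at 10%) rests on an assumed share and on no further gain from iFD in that share. It shows the arithmetic and is not an estimate for this trial. The change is worth making because it is cheap.

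**What to change.** Reword exclusion 4 to cover current CBT in any delivery format (face-to-face, telephone or internet) and current or previous use of the iFD tool. The psychologist who confirms eligibility at the first face-to-face visit can ask about it there.

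In both arms, record within the week 8 medical/psychiatric history already scheduled whether any psychological treatment was started during the trial. Use this for description only, and remove no one from the ITT set because of it.

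The cost is a one-line change to a criterion, one e-CRF item, a few more screen failures and slightly narrower eligibility. If the full protocol already contains such a rule, the sponsor need only state it where the criteria are listed.
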